## Abstract

**Background::**

Neck pain is a common complaint in the general population. Despite the consistent ongoing pain and the resulting economic burden on affected individuals, there have only been a few studies investigating the treatment of acute neck pain. This study aims to evaluate the effectiveness, safety, and cost-effectiveness of the motion style acupuncture treatment (MSAT) and acupuncture treatment for acute neck pain.

**Methods::**

This 2-armed, parallel, multi-centered randomized controlled trial will be conducted at 4 community-based hospitals in Korea. A total of 128 subjects will be randomly assigned, at a 1:1 ratio, to the MSAT and the acupuncture treatment groups. Treatment will be administered 2 to 3 times a week for 2 weeks. The primary outcome will be the visual analog scale of neck pain on movement. The secondary outcomes will be the numeric rating scale of the neck, neck disability index, Northwick Park questionnaire, patient global impression of change, range of motion of the neck, 5-level EuroQol-5 dimension, 12-item Short-Form Health Survey, and EuroQol visual analogue scale. This protocol has been registered at the Clinicaltrials.gov (NCT04539184).

**Discussion::**

To our knowledge, this study is the first well-designed multi-centered randomized controlled trial to evaluate the effectiveness, safety, and cost-effectiveness of MSAT on acute neck pain. The results of this study will be useful for clinicians in primary medical institutions that frequently treat acute neck pain patients and for policymakers working with national health insurance.

## Introduction

1

Neck pain is one of the common musculoskeletal disorders in the general population. Although the prevalence of neck pain varies by studies conducted and the time period, the 1-year prevalence rate is reportedly 25.8%^[1]^ and the prevalence in an adult's lifetime is 50%.^[2]^ Neck pain can develop into considerably severe pain, disability, and cause a financial burden.^[3]^ Years lived with disability from neck pain per 100,000 population was reportedly 352 from 1990 to 2017,^[4]^ and the neck pain was the fourth main cause of years lived with disability according to the 2016 Global Burden of Disease.^[5]^

Among the different types of neck pains, acute neck pain is considered a self-limiting disorder and adults can experience pain during typical activities (e.g., lifting, twisting, and stretching). Acute neck pain is caused by loads applied internally to the tissues or external loads such as a fall and direct impact to the head or neck. However, little is known about the prevalence and treatment of acute neck pain, especially those not caused by whiplash. Vernon et al^[6]^ reported that the point prevalence of acute neck pain to be around 10%. There is currently no consensus for the definition of acute neck pain but is often defined as pain that does not last for more than 4 weeks.^[7,8]^ There is no standardized guideline for the treatment of acute neck pain but in a study of patients that visited general practitioners for acute neck pain in the Netherlands, 42% of patients were prescribed non-steroidal anti-inflammatory drugs and muscle relaxation.^[9]^ In addition, other studies have reported on the effectiveness of laser therapy^[10]^ and cervical spine thrust manipulation^[11]^ on acute neck pain.

The motion-style acupuncture technique (MSAT), which combines traditional acupuncture and movement therapy, is a treatment that induces passive and active movements of the patient with the needles inserted, after a traditional acupuncture treatment. All movements are made under the observation and guidance of a physician. MSAT has been increasingly used to relieve musculoskeletal pain in Korean clinical practice and recently has gained attraction in China as a method to enhance the effect of traditional acupuncture treatment.^[12–14]^ However, the supporting evidence and data for the effectiveness and safety of MSAT are insufficient as only a few related studies have been conducted.

Recently, the combination of MSAT and integrative Korean medicine treatment was reported to be effective for rapid pain reduction and range of motion (ROM) improvement in patients with pain in the cervical spine region due to acute whiplash injury.^[15]^ However, the study was only conducted for patients with a whiplash injury due to a traffic accident and the effectiveness of MSAT alone could not be examined since it was in a combination with the integrative Korean medicine treatment. Therefore, this 2-parallel, multi-centered randomized trial has been designed to evaluate the effectiveness, safety, and cost-effectiveness of MSAT and acupuncture treatment for acute neck pain that has not been caused by whiplash injury.

## Methods

2

### Study design and setting (Fig. 1 and Table 1)

2.1

This 2-armed, parallel, multi-centered randomized controlled trial (RCT) will be conducted at four community-based hospitals in Korea; Jaseng Hospital of Korean Medicine, Daejeon Jaseng Hospital of Korean Medicine, Bucheon Jaseng Hospital of Korean Medicine, and Haeundae Jaseng Hospital of Korean Medicine. A total of 128 patients, 64 for the MSAT and 64 for the acupuncture treatment groups, will be recruited from the 4 hospitals. Treatment will be performed 2 to 3 times a week for 2 weeks, followed by a follow-up for 8 weeks after randomization (Fig. 1).

**Figure 1 F1:**
[figure not shown]
Study flow diagram.

**Table 1 T1:**
[figure not shown]
The timeline of participants^∗^.

The study protocol was approved by the institutional review board (IRB), at each of the institutions, before initiating the participant recruitment process (JASENG 2020-07-014, JASENG 2020-07-015, JASENG 2020-07-016, and JASENG 2020-07-017). The protocol has been registered at the Clinicaltrials.gov (NCT04539184). Information regarding the healthcare institutions and investigators can be found on the clinical trial registration website.

### Participants

2.2

#### Inclusion criteria

2.2.1

1)Neck pain onset or worsening within 1 month2)Visual Analog Scale (VAS) of neck pain on movement or at rest of 5 or higher3)Age between 19 and 70 years old4)Participants that provided informed consent

#### Exclusion criteria

2.2.2

1)Participants diagnosed with a serious disease that can cause pain (e.g., Migration of cancer reaching to spine, fracture of the spine, and dislocation of the spine)2)Progressive neurologic deficits or severe neurologic deficits3)Participants diagnosed with a soft tissue disease that can cause pain (Cancer, fibromyalgia, rheumatoid arthritis, or goat)4)Presence of chronic diseases (e.g., Cardiovascular disease, kidney disease, dementia, diabetic neuropathy, or epilepsy)5)Participants on steroids, immunosuppressants, or psychotropic medication6)Participants who are inadequate or unsafe for acupuncture (e.g., Hemorrhagic disease, severe diabetes, or taking the anticoagulant drug)7)Participants that took NSAIDs or underwent acupuncture treatment within the last 3 days8)Participants that had undergone cervical surgery within the last 3 months9)Participants that had a traffic accident within a month10)Pregnant women or women who planned to conceive11)Participants that had participated in another clinical trial within 1 month or planned to participle in other trials within 6 months of the enrollment12)Participants that could not provide informed consent13)Participants that found it difficult to participate in the trial according to the investigator's decision

The patient may be dropped in clinical trials in the case of an unexpected risk or serious adverse events are occurred. The PI would make the final decision if to drop the patient.

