### Blinding

2.9

Due to the nature of the intervention in this study, it is impossible to blind the physicians and patients. However, in this study, the statistical analysis manager and the outcome assessor will be blinded to secure objectivity and reduce the bias as much as possible. Outcome assessment will be performed in a separate space before the treatment is performed by an assessor, who will not participate in the treatment and does not know the patient's group assignment, and has received standardized training for the data collection procedures.

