### Statistical analysis

2.11

This study will be a randomized controlled study that analyzes the pain intensity scale, functional scale, quality of life, and costs data results of patients who meet the selection criteria.

The primary analyses will be the intention-to-treat analysis, which evaluates those who have received treatment at least once, and the per-protocol analysis, which evaluates only those who have successfully completed the clinical study, excluding those who have been dropped out; the 2 analyses will be performed concurrently.

For processing the missing values, multiple imputations using the Markov Chain Monte Carlo method will be used as the primary method, and 20 imputed datasets will be generated. In addition, the last observation carried forward method will be used for the sensitivity analysis.

The sociodemographic characteristics and treatment expectancy of the subjects will be evaluated for each of the groups. Continuous variables will be represented as mean (standard deviation) or median (quartiles), and categorical variables will be represented as a frequency (%).

The effectiveness endpoint of this clinical trial will be the difference in the amount of change between baseline and each time point by the group for the continuous outcomes (NRS, VAS, NDI, NPQ, EQ-5D-5L, and SF-12). Analysis of Covariance will be performed using the baseline values of each variable as covariates and the group as a fixed factor.

For the sensitivity analysis, datasets without the imputed values will be used to analyze the degree of change from the baseline. The mixed-effects repeated measures analysis will be performed for the primary and secondary outcomes at all time points. The time variable will be included as a categorical variable and the interaction terms of group and time will be included at each time point to evaluate the difference in the effectiveness of MSAT.

To compare the total amount of difference between 2 groups for each outcome within the treatment period (2 weeks) and the entire study period (8 weeks), the areas under the curve (AUC) within each period after randomization will be calculated. The difference in AUC between the 2 groups will be compared using the independent student *t* test.

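### The plan lets patients be dropped from the trial, not only from treatment, after a serious adverse event or unexpected risk, and does not secure their later outcome and safety data

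*Protocol article*

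**What the plan says.** Section 2.2.2, after the list of exclusion criteria, contains the only rule on removing a patient who has come to harm: "The patient may be dropped in clinical trials in the case of an unexpected risk or serious adverse events are occurred". It is followed by: "The PI would make the final decision if to drop the patient". No criteria guide that decision, and stopping the study intervention is not distinguished from leaving the study.

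Four other places bear on what happens next.

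- **Blinding (2.9).** The article states that "it is impossible to blind the physicians and patients". The statistical analysis manager and the outcome assessor are the only people named as blinded.
- **Analysis sets (2.11).** One primary analysis is "the intention-to-treat analysis, which evaluates those who have received treatment at least once". The other, per-protocol, "evaluates only those who have successfully completed the clinical study, excluding those who have been dropped out". Both are run concurrently.
- **Missing data (2.11).** The main approach to incomplete data reads: "multiple imputations using the Markov Chain Monte Carlo method will be used as the primary method, and 20 imputed datasets will be generated". Carrying forward each patient's last observation serves as a sensitivity analysis. An analysis without imputed values and a mixed-effects repeated measures model are also planned.
- **Adverse events (2.12).** All events during the trial are to be recorded and graded. The severity scale depends partly on how the event ended: resolution after treatment belongs to the moderate grade, sequelae to the severe grade.

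**The concern.** Stopping the intervention and leaving the trial are different events. A patient can stop treatment and still mark a VAS at week 3 and week 8. When harm is a reason to leave the trial, the data most likely to be lost belong to the patients in whom the treatment may have gone badly.

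Two things are at stake. The first is safety, which is a stated aim. In a trial of 128 patients a handful of serious events could be the core of the safety result, and grading them on the trial's own scale requires knowing how they ended. The second is the week-3 comparison. Outcomes would be missing for a reason linked to harm, and the reason could differ by arm. The removal is discretionary, and the principal investigator is not among those named as blinded, so the decision could be made with the allocation known.

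**Working it through.** **1. What dropped means in this article.** Section 2.2.2 speaks of dropping a patient from the trial. Section 2.11 sets those who successfully completed the study against those who dropped out. Read together, a patient dropped under section 2.2.2 is a non-completer. Neither those sections nor 2.4.1 (VAS schedule), 2.12 (adverse events) or 2.16 (care after harm) provides for assessment after a drop. Section 2.16 offers medical care and compensation, which is not data collection.

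**2. Path of such a patient through the analysis.**

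- Treated at least once, so in the intention-to-treat set.
- If assessments end at the drop, week-3 VAS is missing and is multiply imputed. The imputation draws on the patient's own observed values (baseline, perhaps visits 4 and 7) and on relationships estimated from patients with observed outcomes. In its usual form it assumes data missing at random; the article does not write the assumption out.
- Excluded from the per-protocol set.
- Under last observation carried forward, the carried value may precede the event. The non-imputed analysis and the mixed model rest on assumptions similar to those of multiple imputation. None of these analyses treats a drop after harm differently.

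**3. The plan's own figures (section 2.6), as the yardstick.** With effect size 0.55, two-sided α = 0.05 and 80% power, the noncentral t calculation gives 53 per arm (power 0.801), 106 in total. The ANCOVA correction is 106 × (1 − 0.24²) = 99.9, so 100. Allowing for 20% dropout, 100 / 0.80 = 125. The next multiple of 8 (4 sites × 2 arms) is 128. The stated 128 reproduces and this point does not affect it.

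**4. Possible size in the primary estimate.** The article gives no serious adverse event rate and no SD, so what follows rests on assumptions. If only one arm is affected, the shift in the group difference is the share dropped × the gap between true and imputed week-3 VAS.

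On the mm scale, assume 2 to 5% dropped, a gap of 20 mm and an SD of 20 mm:

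- Planned difference: 0.55 × 20 = 11 mm.
- Shift: 0.02 × 20 = 0.4 mm (0.4 / 11 = 3.6%) to 0.05 × 20 = 1.0 mm (1.0 / 11 = 9.1%).
- Standard error of the difference with 64 per arm: 20 × √(2/64) = 3.5 mm. The shift is about 0.1 to 0.3 standard errors.

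On the SD scale, with k of 64 patients dropped in one arm and a gap of D SD, the shift is (k/64) × D:

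| k | D | Shift (SD) | Share of 0.55 |
|---|---|---|---|
| 1 | 1 | 0.016 | 2.8% |
| 3 | 1 | 0.047 | 8.5% |
| 6 | 2 | 0.188 | 34% |

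The last row is an extreme case. With one to three such patients and a 1 SD gap, the shift stays below a tenth of the planned effect.

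**The case against.** The strongest case against is that nothing in the article says follow-up stops. The rule is permissive, section 2.12 promises to record all events during the trial, and its severity grades presuppose some knowledge of how an event ended. Follow-up after withdrawal is routine content of a full protocol, and a condensed article may leave it out.

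Much of this stands. A reader might infer that harmed patients do lose their outcome and safety follow-up; the article does not support that. It supports only that continued collection is not secured. The point nevertheless does not rest on silence alone: the article states a rule, and that rule makes harm a reason to leave the trial. A promise covering events during the trial does not clearly reach a patient who is no longer in it.

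A reader might also infer that multiple imputation simply gives such patients the values of those who carried on. It also uses the patient's own earlier scores. The planned sensitivity analyses are not all alike either: in a condition that the introduction calls self-limiting, carrying forward an early pain score will often give a worse value, which is the direction a harmed patient might warrant.

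Nor do the documents support a claim that bias favours the arm with more harm. A serious event need not involve the neck or be caused by treatment, so week-3 neck VAS need not be worse than predicted.

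Finally, excluding dropouts is what a per-protocol set normally does, so that element adds little by itself.

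**Conclusion.** The concern holds in a limited form. As worded, section 2.2.2 permits removal from the trial after harm, at one person's discretion and without blinding of physicians or patients, and section 2.11 counts such patients as non-completers. Their week-3 and week-8 outcomes and the later course of the event are therefore not secured.

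The numerical effect on the primary estimate is probably minor and its direction is not established. The 0.4 to 1.0 mm range depends entirely on an assumed drop rate, gap and SD, and on the drops falling in one arm. The weight of the point lies in the safety data, where no size can be given from the documents, and in the discretionary removal. It is a worthwhile and inexpensive improvement, not a flaw that threatens the trial's main conclusion.

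**What to change.** Reword the last paragraph of section 2.2.2 so that the principal investigator's decision concerns stopping study treatment. Add that, unless the patient withdraws consent, the scheduled week-3 and week-8 assessments and adverse-event follow-up continue, and that the values observed after stopping treatment are used in the intention-to-treat analysis. When treatment should be stopped remains a clinical decision, which this change leaves as it is.

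A sensitivity analysis that does not assume missing at random could be added for patients whose outcomes are still missing after harm.

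The cost is a sentence or two of protocol text and following a few patients through visits that are already planned. The VAS is patient-reported, so collecting it requires no further study treatment. The sample size does not change.

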### Interventions

2.3

All treatments, including the MSAT and acupuncture treatment, will be administered by Korean medicine doctors who have more than 3 years of clinical experience and received standardized training on both the Korean medicine treatment and MSAT. All treatments will be carried out for a total of 2 weeks.

#### Experimental group: MSAT

2.3.1

The protocol for trapezius MSAT is as follows; the patient sits on a chair or the floor, straightens from low back up to the neck, pulls their chin slightly toward the body, and directs their gaze towards the front. In this position, the physician rotates the neck alternately from left to right with 3 disposable needles (30 mm ∗ 0.25 mm; Dong-bang Acupuncture, Korea) inserted into the upper trapezius on both sides of the subject at a depth of about 5 to 10 mm. The neck movement range shall only be up to the ROM and the physician examines whether there is a difference from the normal ROM and presence of other abnormalities in the movement. When the side with the smaller left-to-right ROM is set as the affected side, the left-to-right turning motion is performed regarding the ROM on the affected side. At this time, with the midline of the body as the reference, the patient breathes in when moving closer to the midline and breathes out when moving away from the midline. The above movements are repeated 8 to 10 times and the physician examines whether the movement of the patient's head and neck area is normal. In case of a problem with the movement, the physician guides the patient by placing 1 hand on the posterior cervical region and the other hand on the face, thereby correcting the movement. After completing the repetitive movements, the maximum ROM is checked again and if it does not achieve normal ROM, the left-to-right turning motion is repeated. The procedure continues for a specified treatment time (within 15 minutes) and at the discretion of the physician, the treatment process could either be continued or undergo only the movement therapy or the acupuncture treatment without movement (additional acupoints if necessary) after the treatment process.

A total of 6 treatments will be performed 3 times a week for 2 weeks; however, depending on the patient's condition or circumstances, a total of 4 to 6 treatments for trapezius MSAT may be performed during 2 weeks.

#### Active control group: acupuncture

2.3.2

The protocol for trapezius acupuncture is as follows; Acupuncture points are selected from primary meridians (SI15, TE15, and LI16 bilateral) and extraordinary meridians (GB20, BL10, SI14 bilateral, and GV14 unilateral) on the bilateral upper and middle trapezius according to the physician's discretion. Acupuncture is performed with needles inserted into 6 to 12 selected points. Disposable needles (30 mm ∗ 0.25 mm; Dong-bang Acupuncture, Korea) are used for the insertion, and depending on the characteristics of the acupuncture point, after the perpendicular or oblique insertion, a twirling method is performed for the patient to feel the acupuncture sensation.

A total of 6 treatments will be performed 3 times a week for 2 weeks; however, depending on the patient's condition or circumstances, a total of 4 to 6 treatments may be performed when conducting the treatment twice a week. Duration for the needle insertion will be approximately 15 minutes.

#### Relevent concomitant care

2.3.3

All treatments (drugs, surgery, nerve block, acupuncture, physical therapy, etc.) for relieve neck pain are prohibited until the 3^rd^ week (visit 9), the primary endpoint in both MSAT and control groups. There are no treatment restrictions during the f/u period after the primary endpoint. However, during the study period, acetaminophen (maximum 4 g per day) will be allowed to all subjects and the use of the drug will be recorded in a self-report method.

### Outcome

2.4

#### Primary outcome: visual analogue scale on movement (VAS on movement)

2.4.1

The primary outcome of this study will be the difference between the baseline (Week 1) and the primary endpoint, week 3 (visit 8) for the neck pain felt during movement. The VAS is an assessment tool on which the patient indicates the level of pain along a continuous line of 100 mm in length, with one end indicating no pain and the other indicating the worst pain possible.^[16,17]^

The VAS of neck pain felt on movement will be measured 7 times in total; at the screening, baseline, the last visit of each week during the intervention period (visits 4 and 7), week 3 (visit 8), and week 8 (visit 9).

#### Secondary outcomes

2.4.2

##### Visual analogue scale at rest (VAS at rest)

2.4.2.1

The VAS of neck pain felt at rest will be measured 6 times in total; at the baseline, the last visit of each week during the intervention period (visits 4 and 7), week 3 (visit 8), and week 8 (visit 9).

